**Study rationale**

Human immunodeficiency virus (HIV)-related mortality has dropped significantly due to effective antiretroviral therapy. Epidemiological data suggest a less than 5% ten-year mortality for patients treated with anti-retroviral therapy (ART) (1). As a result of the reduction in early AIDS-related deaths, HIV has become a chronic disease manifesting the common components of chronic disease such as inflammation (2, 3), vascular dysfunction (4-6), and oxidative stress (7, 8). The combination of these adverse factors put HIV patients at increased risk of myocardial infarction (9) compared with age-matched subjects over the long term. A portion of this adverse cardiovascular risk has been linked to therapies necessary to survival in HIV. Several studies suggest that early protease inhibitors might increase the risk of myocardial infarction (10). The leading theory linking early PIs to myocardial infarction stemmed from the relationship between protease inhibitor use and the onset of an atherogenic dysmetabolism including the development of insulin resistance, dyslipidemia, and oxidative stress (11-14). With the advent of newer PIs, and the avoidance of certain NRTIs, the issue of lipodystrophy and insulin resistance has largely been resolved (15).

In contrast to the older protease inhibitors, atazanavir induces neither insulin resistance (16) or dyslipidemia (17). In addition, atazanavir has a property unique among protease inhibitors: elevation of unconjugated bilirubin by inhibiting the enzyme uridine diphosphate glucuronyltransferase (UGT) 1A1 (18). Bilirubin, thought to be solely a waste product, is a potent intracellular antioxidant and may provide a cardiovascular protective effect (19, 20). We have demonstrated that higher levels of bilirubin within the normal range are associated with reduced rates of stroke and peripheral artery disease (21, 22). Patients with Gilbert’s Syndrome (chronic elevations of bilirubin as a result of genetically reduced UGT 1A1) have a lower rate of myocardial infarction compared with age-matched controls (23).

The benefit of atazanavir may be particularly important with the aging of the HIV population. More than 1/4^th^ of all patients with HIV are >50 years of age (24) and the sustained use of ART suggests that the aging of this population will continue, with 50% of the HIV population being older than 50 by 2015. Aging, per se, is an important cardiovascular risk factor and is associated with higher levels of oxidative stress (25-27) and endothelial dysfunction (28). It is plausible that use of atazanavir may improve vascular function through reductions in oxidative stress, ultimately reducing the rate of cardiovascular complications in patients with HIV. Accordingly, we hypothesize that the use of atazanavir in stable HIV patients over the age of 45 years will improve endothelial dysfunction and reduce oxidative stress compared with continuing the current therapy.

**Hypothesis**

We hypothesize that older subjects with HIV randomly assigned to atazanavir will have increased bilirubin levels, reduced oxidative stress, and improved flow-mediated, endothelium-dependent vasodilation compared to subjects not switched to atazanavir.

**Primary Objective**

The primary goal of this study is to determine whether switching to atazanavir will improve vascular endothelial function in older subjects (>45 years) compared to continuing nonatazanavir based therapy.

**Secondary Objectives**

The secondary objective of this study is to determine whether switching to atazanavir reduces oxidative stress, inflammation, and insulin resistance compared with nonatazanavir ART.

In a second analysis, we will recruit 30 stable subjects on atazanavir for more than 6 months meeting the primary objective entry criteria, to perform a single vascular function and metabolic evaluation to determine if chronic atazanavir, when compared to nonatazanavir regimens has lower levels of oxidative stress and improved vascular endothelial function.

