**Trial Population**

Clinically-stable, HIV-infected men and women, 45 years of age or older, who are receiving suppressive ART consisting of co-formulated tenofovir/emtricitabine plus a nonatazanavir/ ritonavir third agent.

For the second protocol, HIV-infected men and women, 45 year of age or older, who are receiving suppressive ART consisting of co-formulated tenofovir/emtricitabine plus atazanavir/ritonavir.

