**Sample Size**

It is estimated that the substitution of atazanavir and increase in bilirubin will increase endothelium-dependent, flow-mediated vasodilation FMD by 3-4%. With an estimated standard deviation of the measurement of 4% and a 1:1 randomization scheme, this yields a power of 81-96% with a sample size of 60 subjects in a parallel design trial.

For aim 2, we expect a similar difference in FMD to be noted between the 30 subjects on atazanavir and the 60 subjects at study entry for the primary aim, thus making the comparison 1:2, yielding a power range of 87-99% to detect a difference in flow-mediated vasodilation.

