**Key Inclusion Criteria**

- Age ≥ 45 years
- Stable non-atazanavir-containing regimen consisting of co-formulated tenofovir/emtricitabine as the NRTIs plus a third agent for 3 months or longer. The third agent can be any FDA-approved PI, NNRTI, or raltegravir.
- HIV RNA < 50 cop/mL at screening and at least once within the prior year,
- No treatment interruptions > 7 days in the 3 months prior to study entry

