**Key Exclusion Criteria**

- Prior treatment failure on or intolerance to atazanavir
- Known or suspected resistance to atazanavir
- Patients with Gilbert’s Syndrome or elevated bilirubin levels (> 1.5 mg/dL) at baseline (for the randomized trial)
- Receiving ART different from co-formulated tenofovir/emtricitabine plus third agent (PI, NNRTI, or raltegravir) regimen
- Current receipt of proton-pump inhibitor therapy
- Recent initiation of hormones or immunomodulators

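### Aim 2 eligibility is inconsistently drafted, and as written subjects with Gilbert's Syndrome can enter the atazanavir group but not its comparator

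*Protocol*

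**What the plan says.** Four protocol sections bear on who may enter the aim 2 cohort.

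- **Secondary Objectives:** "we will recruit 30 stable subjects on atazanavir for more than 6 months meeting the primary objective entry criteria". No exception is stated.
- **Trial Population:** the randomised trial takes people on "co-formulated tenofovir/emtricitabine plus a nonatazanavir/ ritonavir third agent". A separate paragraph for the second protocol takes people aged 45 or older who are "receiving suppressive ART consisting of co-formulated tenofovir/emtricitabine plus atazanavir/ritonavir". It gives no minimum time on atazanavir.
- **Key Inclusion Criteria:** "Stable non-atazanavir-containing regimen consisting of co-formulated tenofovir/emtricitabine as the NRTIs plus a third agent for 3 months or longer". This is the only inclusion list, and it does not say which part of the study it serves.
- **Key Exclusion Criteria:** one line names Gilbert's Syndrome and continues "or elevated bilirubin levels (> 1.5 mg/dL) at baseline (for the randomized trial", where the parenthesis closes. No other line in either list is limited to one part of the study.

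The Data and Statistical Plan compares the 30 atazanavir subjects with the baseline values of the 60 randomised subjects, using a between-subject t test and no stated adjustment. The Sample Size section describes this as "thus making the comparison 1:2, yielding a power range of 87-99% to detect a difference in flow-mediated vasodilation".

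**The concern.** Aim 2 is not randomised. Its comparability rests mainly on the two groups being selected by the same rules, apart from the exposure under study. The protocol imports the randomised trial's criteria wholesale in one place, contradicts one of them through the cohort's own definition, and waives another elsewhere. A site has to infer which criteria carry over.

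The waiver matters most. The line limited to the randomised trial covers two different things. One is a laboratory value that atazanavir itself raises, through "elevation of unconjugated bilirubin by inhibiting the enzyme uridine diphosphate glucuronyltransferase (UGT) 1A1". The other is an inherited condition present before any treatment. Waiving the first is needed if the cohort is to represent people on atazanavir. Waiving the second admits to one group only a type of subject whom the Study rationale describes as having lifelong high bilirubin and a lower rate of myocardial infarction. Part of any FMD difference could then reflect who was let in and not what they were taking.

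**Working it through.** **Step 1. Criteria side by side.**

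| Item | Randomised trial (source of the 60 comparators) | Aim 2 cohort, Secondary Objectives taken literally | Aim 2 cohort, other sections |
|---|---|---|---|
| Third agent | Not atazanavir | On atazanavir, yet must meet the non-atazanavir criterion | Atazanavir/ritonavir (Trial Population) |
| Time on regimen | 3 months or longer | More than 6 months | Not stated (Trial Population) |
| Bilirubin above 1.5 mg/dL | Excluded | Excluded by import | Not excluded (Key Exclusion Criteria) |
| Gilbert's Syndrome | Excluded | Excluded by import | Not excluded (Key Exclusion Criteria) |

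The first row is a contradiction in wording. Trial Population resolves the intent. In the third and fourth rows the specific limit in Key Exclusion Criteria is the better guide, because it is the section that sets the rule.

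**Step 2. Follow the better-supported reading.** The regimen criterion falls away for aim 2, and the whole Gilbert's/bilirubin line applies to the randomised trial only. The 60 comparators then contain no known Gilbert's Syndrome, while the 30 atazanavir subjects may. This asymmetry remains after the charitable reading has removed the other difficulties.

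**Step 3. Direction.** The Study rationale describes Gilbert's Syndrome as chronic bilirubin elevation from reduced UGT 1A1 with fewer myocardial infarctions, and the Hypothesis ties higher bilirubin to better FMD. On the protocol's own reasoning the asymmetry favours atazanavir.

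**Step 4. Size (illustration).** The documents give neither the prevalence of Gilbert's Syndrome nor its effect on FMD, so both are assumed.

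- Prevalence 3% to 10%: 0.03 × 30 = 0.9 and 0.10 × 30 = 3, so about 1 to 3 subjects.
- FMD higher by 4 points in those subjects. Shift in the group mean = (number / 30) × 4, which is 1/30 × 4 = 0.13 and 3/30 × 4 = 0.4 points.
- Against the planned difference: 0.4/4 = 10% and 0.4/3 = 13% at the upper end.
- Standard error of the difference with the protocol's SD of 4: 4 × √(1/30 + 1/60) = 0.89. The upper shift is 0.4/0.89 = 0.45 standard errors. If there were no true difference, a two-sided 5% test (alpha assumed; none is stated) would reject with probability Φ(−1.96 + 0.45) + Φ(−1.96 − 0.45), about 0.065 + 0.008 = 7.3%. At the lower shift (0.13/0.89 = 0.15) it is about 5.3%.

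**Step 5. The stated power.** For 30 against 60, SD 4 and two-sided 5%, a t test has power 91.3% for a 3-point difference and 99.3% for 4 points. The protocol gives 87-99%, so the upper end is reproduced and the lower is not. That is a separate matter and does not bear on eligibility. It does show what a small loss costs: with 28 against 60, power at 3 points is 90.0%.

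**The case against.** The strongest reply is that the intent is plain. Trial Population has its own paragraph for the second protocol, the cohort sentence requires atazanavir, and the analysis section refers to subjects stable on it. The specific text governs the general import, so the sentence means that the remaining criteria apply. This stands, and it disposes of three stronger claims that a reader might infer:

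- **That nobody is eligible for aim 2.** This follows only if Trial Population is ignored.
- **That the 1.5 mg/dL limit would remove the subjects in whom atazanavir acted.** Secondary Objectives set no limit of their own, and the section that does sets it for the randomised trial.
- **That the sections contradict each other on ritonavir.** Neither criteria list requires or forbids ritonavir boosting for this cohort. Secondary Objectives are merely less specific than Trial Population, and the two read together give atazanavir/ritonavir for more than 6 months.

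On Gilbert's Syndrome, the reply is that the waiver is explicit and so deliberate, that the cited link is with myocardial infarction and not FMD, and that few subjects are affected. The last two points are fair and limit the size. The first does not remove the asymmetry. One could also attach the parenthesis to the bilirubin value alone, which would keep Gilbert's Syndrome excluded throughout. The wording does not settle this, which is itself a reason to split the line.

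A further reply is that an analysis plan, not shown here, could adjust. With no known cases among the comparators, an indicator for Gilbert's Syndrome would in effect set the affected atazanavir subjects aside, so adjustment amounts to excluding them after enrolment.

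**Conclusion.** The point holds in limited form. The sections on aim 2 eligibility conflict in wording and should be reconciled, although the intended population can be recovered. The substantive fault is that Gilbert's Syndrome is waived along with the bilirubin value. This permits a one-sided selection difference in a non-randomised comparison with no stated adjustment.

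The expected direction favours atazanavir, inferred from the protocol's own rationale. The size is unknown and probably small: about 0.1 to 0.4 FMD points if 1 to 3 of 30 subjects are affected and each is 4 points higher, neither of which the documents give. The randomised primary comparison is untouched. The documents do not support saying that aim 2 cannot recruit or that its result would be overturned. The correction is worth making because it is cheap and removes an avoidable alternative explanation.

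**What to change.** 1. In Secondary Objectives, state that aim 2 subjects meet the same criteria as the randomised trial except the non-atazanavir regimen and the on-treatment bilirubin limit.
2. In Key Exclusion Criteria, split the line: one entry for known Gilbert's Syndrome, worded so that the same criterion governs both groups being compared, and one for bilirubin above 1.5 mg/dL, limited to the randomised trial. Since the comparators come from a trial that excludes Gilbert's Syndrome, equal treatment means applying that exclusion to the aim 2 cohort too.
3. While editing, carry the 6-month minimum and the ritonavir wording consistently through Secondary Objectives and Trial Population. What the sponsor chooses there is a clinical matter; the sections need only agree.

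The cost is protocol wording and perhaps a few aim 2 candidates with known Gilbert's Syndrome to replace.

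One limitation remains and should be stated. Atazanavir and Gilbert's Syndrome both reduce UGT 1A1 activity, so bilirubin measured on atazanavir may not identify undiagnosed cases, whereas the 1.5 mg/dL limit can still remove such people from the comparator. The change reduces the asymmetry but does not abolish it.

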**Treatment**

On entry to the study, patients will be randomized to continue their current “key third drug” component of ART or to substitute atazanavir 300 mg daily with ritonavir 100 mg daily (to be taken with food) for 28 days. All patients will continue to receive ongoing co-formulated tenofovir/emtricitabine.

**Trial Population**

Clinically-stable, HIV-infected men and women, 45 years of age or older, who are receiving suppressive ART consisting of co-formulated tenofovir/emtricitabine plus a nonatazanavir/ ritonavir third agent.

For the second protocol, HIV-infected men and women, 45 year of age or older, who are receiving suppressive ART consisting of co-formulated tenofovir/emtricitabine plus atazanavir/ritonavir.

**Sample Size**

It is estimated that the substitution of atazanavir and increase in bilirubin will increase endothelium-dependent, flow-mediated vasodilation FMD by 3-4%. With an estimated standard deviation of the measurement of 4% and a 1:1 randomization scheme, this yields a power of 81-96% with a sample size of 60 subjects in a parallel design trial.

For aim 2, we expect a similar difference in FMD to be noted between the 30 subjects on atazanavir and the 60 subjects at study entry for the primary aim, thus making the comparison 1:2, yielding a power range of 87-99% to detect a difference in flow-mediated vasodilation.

**Key Inclusion Criteria**

- Age ≥ 45 years
- Stable non-atazanavir-containing regimen consisting of co-formulated tenofovir/emtricitabine as the NRTIs plus a third agent for 3 months or longer. The third agent can be any FDA-approved PI, NNRTI, or raltegravir.
- HIV RNA < 50 cop/mL at screening and at least once within the prior year,
- No treatment interruptions > 7 days in the 3 months prior to study entry

**Key Exclusion Criteria**

- Prior treatment failure on or intolerance to atazanavir
- Known or suspected resistance to atazanavir
- Patients with Gilbert’s Syndrome or elevated bilirubin levels (> 1.5 mg/dL) at baseline (for the randomized trial)
- Receiving ART different from co-formulated tenofovir/emtricitabine plus third agent (PI, NNRTI, or raltegravir) regimen
- Current receipt of proton-pump inhibitor therapy
- Recent initiation of hormones or immunomodulators

**Study Assessments**

Evaluation of vascular function in conduit vessels: Vascular function of the brachial artery will be measured in all subjects as reported previously by the applicants and as recommended by a recent task force (29, 30). To assess endothelium-dependent vasodilation, measurements of brachial artery diameter will be made under basal conditions and during reactive hyperemia following five minutes of an ischemic stimulus applied by sphygmomanometric cuff. Reactive hyperemia increases brachial artery blood flow. Flow is a physiologic stimulus that releases nitric oxide from the endothelium. Forearm ischemia will be induced by inflating a blood pressure cuff to suprasystolic pressures for 5 minutes. This results in vasodilation of the downstream resistance vessels. Following release of the cuff, there is a 5 to 8-fold increase in flow through the brachial artery, i.e., reactive hyperemia. We have found that the maximal increase in brachial artery diameter occurs at one minute of reactive hyperemia and that this dilation is mediated by nitric oxide (31). Endothelium-independent vasodilation will be assessed by measuring brachial artery diameter under basal conditions and 3 minutes following the administration of sublingual nitroglycerin (0.4 mg) (32). Maximal brachial artery dilation occurs 3 to 4 minutes after the administration of sublingual nitroglycerin. We have found that this technique yields an interobserver variability of 0.05±0.16% and intraobserver variability of 0±0.15%.

**Correlative Studies**

We will measure blood-based markers of oxidative stress (myeloperoxidase, malondialdehyde, and bilirubin), inflammation (high sensitivity C-reactive protein and tumor necrosis factor alpha receptor 2), and insulin resistance (fasting insulin and glucose). Each of these tests will be correlated with baseline and change in vascular function.

**Data and Statistical Plan**

[figure not shown]
The primary endpoint of this study will be endothelium-dependent, flow-mediated vasodilation of the brachial conduit artery in subjects randomized to atazanavir compared with subjects continuing their current therapy. Nitroglycerin-mediated, endothelium independent vasodilation will be a secondary endpoint. The analysis begins with descriptive and graphical summaries of each outcome measure at pre-treatment, treatment at 7 days, and post treatment and difference from pre to post treatment. The assessment of the normality of each outcome will be performed by plotting the raw data and transformation will be applied if necessary. The primary analysis of between-subject effects will be assessed using student t tests. Sample size calculation: This protocol will be powered to detect a statistically significant difference in both resistance arteriole and conduit artery studies. We will enroll 60 subjects for the randomized portion of this protocol. Thirty subjects will receive atazanavir and 30 will continue to receive their baseline ART. Nitric oxide accounts for 50-60% of the increase in vasodilation to reactive hyperemia (31). It is anticipated that atazanavir will improve absolute endothelium-dependent vasodilation approximately 3% during flow mediated vasodilation. (Please see the table to see a range of power based on effect.)

Analysis of markers of bilirubin, oxidant stress, inflammation, and insulin sensitivity: As key secondary endpoints, the analysis begins with descriptive and graphical summaries of each outcome measure at pre treatment, post treatment and difference from pre to post treatment. The assessment of the normality of each outcome will be performed by plotting the raw data and transformation will be applied if necessary. The primary analysis of between-subject effect will be assessed using paired student t tests. A Bonferroni correction will be applied to account for multiple comparisons. The relationship between changes in secondary markers and changes in vascular function will be assessed using multivariate analysis of variance (MANOVA).

For the second protocol, vascular function for the 30 subjects stable on atazanavir will be compared to the baseline vascular function of the 60 subjects enrolled for the randomized protocol. The analysis plan, including descriptive and graphical summaries, testing of normality with transformation as needed, and between subject t testing will be applied similarly as in randomized trial.

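### The primary FMD t test names no baseline covariate and does not say whether it tests the post-treatment value or the change; adjusting for baseline FMD would usually gain power at very small cost

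*Protocol*

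**What the plan says.** The Data and Statistical Plan defines the endpoint as follows: "The primary endpoint of this study will be endothelium-dependent, flow-mediated vasodilation of the brachial conduit artery in subjects randomized to atazanavir", compared with subjects who stay on their current therapy. It then lists the descriptive summaries, covering "each outcome measure at pre-treatment, treatment at 7 days, and post treatment and difference from pre to post treatment", and sets the test: "The primary analysis of between-subject effects will be assessed using student t tests". No covariate is named. The quantity that enters the test, end-of-treatment FMD or its change from baseline, is not identified.

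Baseline FMD will be available. Pre-treatment is one of the listed time points, and the second protocol compares its 30 subjects on stable atazanavir with the randomised subjects at entry: their vascular function is to be "compared to the baseline vascular function of the 60 subjects enrolled for the randomized protocol".

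The Sample Size section assumes that atazanavir "will increase endothelium-dependent, flow-mediated vasodilation FMD by 3-4"%, with an "estimated standard deviation of the measurement of 4"%, and reports 81-96% power for 60 subjects. The Data and Statistical Plan gives the split, "Thirty subjects will receive atazanavir and 30 will continue to receive their baseline ART", and anticipates an absolute improvement of about 3%, the lower end of that range. No correlation between pre- and post-treatment FMD is given.

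**The concern.** Baseline FMD is measured before randomised treatment in every subject, and it may well predict FMD 28 days later. A t test on the post-treatment value does not use it, so a chance baseline difference between arms carries into the estimate to the extent that baseline predicts follow-up. With SD 4 and 30 per arm, that chance difference has a standard error of 4 × sqrt(2/30) = 1.03 points, about a third of the anticipated effect. A t test on the change does use baseline, but with a fixed coefficient of 1, which adds noise when the correlation is modest.

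At stake is precision in a small trial. At the 3-point effect that the plan anticipates, the planned power is little above 80%, and the protocol states no allowance for dropout. Leaving the analysed quantity open also means that the power of the planned test depends on which reading is taken.

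**Working it through.** **Inputs.** From the protocol: difference 3 to 4 points, SD 4, 30 per arm. Assumed: two-sided alpha 0.05, because the protocol gives no alpha, and 60 subjects analysed. One-sided 0.05 would give 89.0% and 98.5%, which does not match the stated range. The pre/post correlation ρ is not in the protocol and is varied. The SD is taken to be equal at both time points and in both arms.

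**Step 1: reproduce the stated power.** For a two-sample t test, the noncentrality is δ / (SD × sqrt(2/30)), with 58 degrees of freedom and critical value 2.002.

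- δ = 3: 3 / 1.033 = 2.905, power 81.5%.
- δ = 4: 4 / 1.033 = 3.873, power 96.8%.

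The stated 81-96% is reproduced.

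**Step 2: the SD that each analysis faces**, if 4% is the SD of a single measurement.

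- Post-treatment value: 4.
- Change: 4 × sqrt(2(1 − ρ)). At ρ = 0.3 this is 4 × sqrt(1.4) = 4.73, at 0.5 it is 4.00, and at 0.7 it is 3.10.
- Baseline-adjusted linear model (ANCOVA): 4 × sqrt((1 − ρ²)(1 + 1/56)). The factor 1 + 1/56 is the small-sample inflation from estimating the slope, and 57 degrees of freedom remain. At ρ = 0.3 this is 4 × sqrt(0.91 × 1.018) = 3.85, at 0.5 it is 3.49, and at 0.7 it is 2.88.

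**Step 3: power at a 3-point difference, 30 per arm.**

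| Assumed ρ | t test, post value | t test, change | Baseline-adjusted model |
|---|---|---|---|
| 0 | 81.5% | 52.4% | 80.8% |
| 0.1 | 81.5% | 56.7% | 81.2% |
| 0.3 | 81.5% | 67.5% | 84.3% |
| 0.5 | 81.5% | 81.5% | 90.5% |
| 0.7 | 81.5% | 95.8% | 97.7% |

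The adjusted model overtakes the post-value test at ρ of about 0.13. Its largest loss is 81.5 − 80.8 = 0.7 points, at ρ = 0. It beats the change-score test at every correlation shown.

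**Step 4: variance ratios, ignoring the small inflation.** Adjusted against post value is 1 − ρ²: 0.91, 0.75 and 0.51 at ρ = 0.3, 0.5 and 0.7. Adjusted against change is (1 + ρ)/2: 0.65, 0.75 and 0.85. In subjects, the gain over the post-value test is a factor of 1/0.91 = 1.10 at ρ = 0.3 and 1/0.75 = 1.33 at ρ = 0.5.

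**Step 5: the other reading of the SD.** If 4% is the SD of the change, the change-score test has 81.5% power at 3 points whatever the correlation. The adjusted model then has SD 4 × sqrt(((1 + ρ)/2)(1 + 1/56)) and power 93.9%, 90.5% and 86.6% at ρ = 0.3, 0.5 and 0.7.

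**The case against.** The best defence is that nothing here is wrong. A two-sample t test is valid under randomisation for either quantity, it reproduces the stated power, and 81% at the lower planning effect is above the customary 80%. All of that stands, and it is why the point is an improvement only.

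A reader might infer that the primary comparison ignores baseline altogether. The protocol does not settle this. The pre-to-post difference is listed among the summaries shortly before the t test sentence, and the Correlative Studies section refers to change in vascular function, so the test may be on change. What can be said is that no covariate is named and the analysed quantity is open.

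A reader might also infer that the stated power is wrong or fits only a post-value test. The SD wording most naturally describes a single value, but it is loose, and the power table that the text points to is not visible in the copy reviewed. The adjusted model does better than the change-score test on either reading of the SD at ρ of 0.3 to 0.7.

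Finally, the gain depends on a correlation that the protocol does not give. That is correct, so its size is conditional. At ρ = 0.3 the gain over the post-value test is under 3 points, and near zero correlation there is none. Nor does adjustment remove bias from missing outcomes. Covariate adjustment is often left to the SAP, but this protocol itself names the primary test, so the choice is open to comment.

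**Conclusion.** The planned t test is valid and meets its stated power. It can be improved in two respects: it does not say whether post-treatment FMD or the change is tested, and it names no baseline covariate although the baseline value will be in hand for all 60 subjects. With SD 4 for a single measurement, 30 per arm, two-sided 0.05 and a 3-point effect, adjustment raises power over the post-value test by about 3, 9 and 16 points at assumed correlations of 0.3, 0.5 and 0.7 (84.3, 90.5 and 97.7 against 81.5). Over the change-score test the gains are about 17, 9 and 2 points (against 67.5, 81.5 and 95.8). The possible loss is at most 0.7 points, and only below a correlation of about 0.13. The direction is secure for any moderate correlation; the size is not, because the protocol gives no correlation.

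**What to change.** Replace the t test sentence for the primary endpoint with wording such as: The primary analysis is a linear model of end-of-treatment FMD on randomised arm with baseline FMD as covariate; the adjusted difference between arms and its 95% confidence interval are the primary result. Keep the t test as a sensitivity analysis and state whether it is on the post-treatment value or on the change. In the Sample Size section, state whether the 4% is the SD of a single measurement or of the change.

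The cost is wording, one degree of freedom and a variance inflation of about 1/56. No extra subjects, visits or measurements are needed, and the sample size of 60 can stay.

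### The biomarker treatment effect is assigned to paired t tests in an unmatched parallel-group trial; the sentence should name a between-arm test

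*Protocol*

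**What the plan says.** The Data and Statistical Plan makes bilirubin and the markers of oxidant stress, inflammation and insulin sensitivity key secondary endpoints. It summarises each one before treatment, after treatment and as the difference, and then states: "The primary analysis of between-subject effect will be assessed using paired student t tests". A Bonferroni correction follows, without the number of comparisons.

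Other parts of the protocol bear on this sentence:

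- **Design.** Sample Size describes "a sample size of 60 subjects in a parallel design trial". The Data and Statistical Plan adds: "Thirty subjects will receive atazanavir and 30 will continue to receive their baseline ART". No matching or crossover is described.
- **Question.** Secondary Objectives asks "whether switching to atazanavir reduces oxidative stress, inflammation, and insulin resistance compared with nonatazanavir ART".
- **Vascular endpoint.** The matching sentence in the same section reads: "The primary analysis of between-subject effects will be assessed using student t tests". It does not contain the word "paired".
- **Second protocol.** The comparison of 30 subjects already on atazanavir with the 60 trial subjects at baseline uses between-subject t testing.

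**The concern.** A between-subject effect compares different people. A paired test needs two linked values, either from the same person or from matched people. The sentence asks for both, and the design provides no link between the arms.

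The only pairing that the data contain is pre/post within a subject. A literal analyst could therefore run one pre/post test per arm and report which arm changed significantly. That does not estimate the contrast in the secondary objective. Whatever moves both arms alike between the two visits would stay in the atazanavir result, although the control arm exists to remove it.

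**Working it through.** **1. Which test the plan's own power figure implies**

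Inputs from Sample Size: 30 per arm, FMD difference 3% to 4%, SD 4%, stated power 81-96%. Alpha is not stated; two-sided 0.05 is assumed.

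Unpaired t test, 58 df, noncentrality = (difference/SD)/√(2/30):

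- 3%: 0.75/0.2582 = 2.905, power 81.5%
- 4%: 1.00/0.2582 = 3.873, power 96.8%

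This reproduces the stated range to within a point. A paired test on 30 differences with SD 4% has noncentrality 0.75 × √30 = 4.108 and 1.00 × √30 = 5.477, giving 97.8% and over 99.9%, which does not match. The vascular sentence does not say "unpaired", but the power figures show that an unpaired test was intended there. No power is stated for the biomarkers.

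**2. Reading A: pre/post tests within each arm**

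Inputs: n = 30. Correlative Studies lists seven markers (myeloperoxidase, malondialdehyde, bilirubin, C-reactive protein, tumor necrosis factor alpha receptor 2, insulin, glucose). Taking these as seven comparisons is an assumption, giving alpha = 0.05/7 = 0.00714. There is no treatment effect, and both arms share a mean change of δ SD of the change. The protocol gives no value for δ, so a range is shown.

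The test statistic is noncentral t with 29 df and noncentrality δ√30. The two-sided critical value is 2.894 at 0.05/7.

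| δ | δ√30 | Atazanavir-arm test significant |
|---|---|---|
| 0 | 0 | 0.7% |
| 0.1 | 0.548 | 1.5% |
| 0.2 | 1.095 | 4.8% |
| 0.3 | 1.643 | 13% |
| 0.4 | 2.191 | 26% |
| 0.5 | 2.739 | 45% |

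The pattern of significance in the atazanavir arm but not in the control arm has probability p(1 − p). At δ = 0.3 it is 0.126 × 0.874 = 11%, and at δ = 0.5 it is 0.452 × 0.548 = 25%.

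The unpaired test on the change cancels δ. In 40,000 simulated trials at each of δ = 0, 0.25 and 0.5, its error at a nominal 5% was 4.8% to 5.0%.

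**3. Reading B: subjects paired arbitrarily across arms**

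The mean of the 30 differences still estimates the between-arm effect without bias. Degrees of freedom fall from 58 to 29. At a standardised difference of 0.75, power falls from 81.5% to 80.2% at 0.05, or from 54.9% to 51.3% at 0.05/7. The loss is small, but the p-value depends on which subjects are put together.

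**4. Reading C: loose wording for a two-sample test on within-subject differences**

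This analysis is valid. Only the name of the test is wrong.

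**The case against.** The strongest defence is Reading C. The sentence names the between-subject effect as its target, the same paragraph summarises the pre-to-post difference, and the objective is comparative. On that view, "paired" refers to how the change score is formed, and the arms are still compared with each other. This stands as a real possibility, so a reader should not infer that the key secondary question will necessarily be answered without the control arm. The protocol does not establish that.

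Two other strong readings also fail. One is that a paired test cannot compare independent arms at all. Reading B shows that arbitrary pairing, if unrelated to outcome, is unbiased and only slightly less powerful.

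The other is that the false-positive rate on a within-arm reading is 36% to 75%. Those figures come from drifts of 0.3 and 0.5 SD at an uncorrected 0.05. They leave out the Bonferroni correction that the plan applies and the smaller drifts, for which the rates are 1.5% to 4.8%. The drift is itself an assumption: the protocol reports no assay, fasting or visit effect.

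The possible existence of a separate analysis plan does not remove the point. The protocol does not leave the test open. It names one, and the name does not fit the design. The MANOVA does not fill the gap, because it relates marker changes to vascular changes.

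**Conclusion.** The sentence is wrong as written. It assigns a between-arm effect on key secondary endpoints to a test for linked observations, in a trial that has no link between arms, and nothing else in the protocol supplies the correct test for the markers.

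The consequence depends on how the sentence is carried out. With pre/post tests within each arm, the excess over the nominal 0.7% per marker ranges from slight (1.5% at a common drift of 0.1 SD) to serious (45% at 0.5 SD). Those figures rest on seven comparisons, 30 analysed subjects per arm, normally distributed changes and an assumed drift. With no drift the error rate is nominal, but the test still does not address the stated contrast. With arbitrary pairing, the fault is a p-value that depends on the pairing. With loose wording, the fault is confined to the text.

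The primary FMD analysis, its sample size and the second protocol's comparison are not affected.

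**What to change.** Replace the sentence with: Between-arm effects on each biomarker will be assessed with an unpaired (two-sample) t test on the pre-to-post difference, transformed if necessary, with the stated Bonferroni correction.

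ANCOVA of the post-treatment value on arm, adjusted for the baseline value, is preferable and needs no further data, but the defect does not require it. Paired tests may stay as within-arm description.

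The cost is one sentence, with no extra subjects or measurements. It should be settled before the data are analysed, so that the test is not chosen after the results are seen.
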